## Abstract

**Background:**

The COVID-19 pandemic caused by the severe acute respiratory syndrome coronavirus 2 (SARS-CoV-2) continues to evolve as a global health crisis. Although highly effective vaccines have been developed, non-pharmaceutical interventions remain critical to controlling disease transmission. One such intervention—rapid, at-home antigen self-testing—can ease the burden associated with facility-based testing programs and improve testing access in high-risk communities. However, its impact on SARS-CoV-2 community transmission has yet to be definitively evaluated, and the socio-behavioral aspects of testing in underserved populations remain unknown.

**Methods:**

As part of the Rapid Acceleration of Diagnostics–Underserved Populations (RADx-UP) program funded by the National Institutes of Health, we are implementing a public health intervention titled “Say Yes! COVID Test” (SYCT) involving at-home self-testing using a SARS-CoV-2 rapid antigen assay in North Carolina (Greenville, Pitt County) and Tennessee (Chattanooga City, Hamilton County). The intervention is supported by a multifaceted communication and community engagement strategy to ensure widespread awareness and uptake, particularly in marginalized communities. Participants receive test kits either through online orders or via local community distribution partners. To assess the impact of this intervention on SARS-CoV-2 transmission, we will conduct a non-randomized, ecological study using community-level outcomes. Specifically, we will evaluate trends in SARS-CoV-2 cases and hospitalizations, SARS-CoV-2 viral load in wastewater, and population mobility in each community before, during, and after the SYCT intervention. Individuals who choose to participate in SYCT will also have the option to enroll in an embedded prospective cohort substudy gathering participant-level data to evaluate behavioral determinants of at-home self-testing and socio-behavioral mechanisms of SARS-CoV-2 community transmission.

**Discussion:**

This is the first large-scale, public health intervention implementing rapid, at-home SARS-CoV-2 self-testing in the United States. The program consists of a novel combination of an at-home testing program, a broad communications and community engagement strategy, an ecological study to assess impact, and a research substudy of the behavioral aspects of testing. The findings from the SYCT project will provide insights into innovative methods to mitigate viral transmission, advance the science of public health communications and community engagement, and evaluate emerging, novel assessments of community transmission of disease.

**Supplementary Information:**

The online version contains supplementary material available at 10.1186/s12889-021-12007-w.

## Background

The coronavirus disease 2019 (COVID-19) pandemic continues to evolve as a global public health crisis. As of July 2021, 34 million people in the United States have been infected with the SARS-CoV-2 virus, and over 600,000 have died [1]. Infections and deaths have disproportionally affected historically marginalized populations [2–4]. Although multiple highly effective SARS-CoV-2 vaccines have been rapidly developed and are now available, public health measures remain critical to controlling the pandemic [5]. Vaccination rates vary widely by state, with vaccine accessibility, hesitancy, misinformation, and mistrust contributing to incomplete uptake, particularly among historically underrepresented groups [6–9]. Furthermore, the Centers for Disease Control and Prevention (CDC) has recorded more than 10,000 breakthrough infection cases, [10] contributing to vaccine hesitancy. The durability of response to the vaccines is currently unknown, with some of the most recent variants potentially impacting the effectiveness of the vaccines [11, 12]. Also, the effectiveness of the vaccines in certain groups, such as those who are immunocompromised, is still being assessed [13]. With the current reality of vaccination challenges, there continues to be an urgent need to develop novel, effective mitigation measures, such as non-pharmaceutical interventions (NPIs), that prioritize historically underrepresented populations [5].

The availability of rapid tests for detecting SARS-CoV-2 presents opportunities for self-administered, frequent at-home testing in asymptomatic populations as part of a broader NPI strategy, including masking, physical distancing, handwashing, contact tracing, and isolation. Early testing strategies suffered from limited access to testing sites and long wait times for results [14]. Periodic home testing can overcome these barriers by facilitating convenient testing, identifying SARS-CoV-2 index cases early, triggering isolation and quarantine precautions, and ultimately decreasing community transmission [15]. With 50% or more of infections resulting from presymptomatic or asymptomatic transmission, [16] frequent at-home testing may also offer a practical option for screening for and breaking transmission chains. However, previous at-home testing studies have generated inconclusive results due to inadequate community engagement strategies for promoting consistent testing in the target population and limited testing and prevention knowledge, attitudes, and behavior [17, 18]. A public health intervention of frequent at-home testing could ease the burden of large-scale facility-based testing programs, provide communities with an additional course of action to reduce the impact of COVID-19, and catalyze urgent action to address needs in high-risk communities. This type of initiative requires intentional engagement with the community and a clear recognition of the risk of SARS-CoV-2 infection to individuals and the community.

Building on our experience with engaging communities for health interventions, and in partnership with the National Institutes of Health (NIH) and the CDC, we launched a public health intervention titled “Say Yes! COVID Test” (SYCT) to determine whether rapid, at-home testing reduces SARS-CoV-2 community transmission and to explore human behavioral factors affecting viral testing in two counties in the southeastern United States that include underserved populations. This project consists of four components: the at-home testing public health intervention, a broad communication and community engagement strategy, an ecologic study of the effectiveness of the public health intervention, and a research substudy assessing behavioral aspects of home testing. Here we report the design, methods, and ecological analysis of SYCT. A more detailed description of communications and community engagement strategies will be included in future papers.

## Methods/design

### Partnerships

To implement and evaluate the community rollout of SYCT, we leveraged national partnerships in community engagement; clinical trials operations; informatics; data collection, integration, and dissemination; biostatistics; public health; implementation science; and engagement science (Table 1). We collaborated with the NIH, CDC, state and local health departments, and community, research, and corporate partners. We also capitalized on the existing robust infrastructure among the partnering research team, including the Rapid Acceleration of Diagnostics–Underserved Populations (RADx-UP) program, the University of North Carolina (UNC) Center for Health Equity Research, the Duke Clinical Research Institute, Community-Campus Partnerships for Health (CCPH), and North Carolina Central University.

**Table 1 Tab1:** Say Yes! COVID Test (SYCT) program partners and collaborators and their respective roles

Institution	Role
NIH	Study funder; provided test kits, approved protocol, and implementation plans, led SYCT launch, and coordinated study activities among stakeholders
CDC	Assisted with protocol development and selection of SYCT communities, engaged local and state health departments
RADx-UP Coordination and Data Collection Center (Duke Clinical Research Institute and the UNC Center for Health Equity Research)	Led design of SYCT intervention and ecological analysis, consulted on public health intervention protocol development, implementation of community-based distribution; created, designed, and implemented marketing campaign for public health intervention; consulted on design and implementation of community engagement plan; tracked kit distribution from local distribution partners; performed data integration and analysis, and manuscript preparation; responsible for all elements of SYCT substudy design, survey development, data management and analysis, and reporting
NCCU	Assisted with design and implementation of community engagement strategy and identification of local distribution partners
CCPH	Led design and implementation of community engagement plan for SYCT; led engagement and relationship building efforts with local distribution partners
University of Massachusetts	Data management partner for the SYCT substudy
Pitt County (NC) Health Department	Coordinated test distribution and local distribution partner engagement for SYCT in Pitt County, NC
Chattanooga (TN) Health Department	Coordinated test distribution and local distribution partner engagement for SYCT in Chattanooga, TN
Quidel	Manufactured at-home tests; applied for and received emergency use authorization from FDA
CareEvo	Designed the study mobile application; coordinated online ordering portal and distribution of kits via Amazon
Amazon	Distributed test kits requested through an online ordering system
DataRobot	Conducted simulations during planning for the public health intervention to guide community selection
[name] Laboratory (UNC)	Processed and tested wastewater samples from North Carolina
Biobot Analytics, Inc.	Processed and tested wastewater samples from Tennessee

*Abbreviations: CCPH* Community-Campus Partnerships for Health, *CDC* Centers for Disease Control and Prevention, *FDA* US Food and Drug Administration, *NCCU* North Carolina Central University, *NIH* National Institutes of Health, *RADx-UP* Rapid Acceleration of Diagnostics–Underserved Populations, *UNC* University of North Carolina

### Study design

We are performing a non-randomized ecological analysis to assess the impact of the public health intervention consisting of at-home, self-administered SARS-CoV-2 testing (SYCT) on community transmission (Figs. 1 and 2). Specifically, we will use publicly reported SARS-CoV-2 testing, hospitalization, mortality, and vaccination data, augmented by detailed surveillance data from the health departments on community SARS-CoV-2 transmission. In addition, SARS-CoV-2 wastewater testing will be performed.

**Fig. 1 Fig1:**
[figure not shown]
Schematic of Say Yes! COVID Test program components

**Fig. 2 Fig2:**
[figure not shown]
Timeline of Say Yes! COVID Test program activities and data collection

Individuals who chose to participate in the SYCT intervention could also enroll in the embedded prospective cohort substudy. The SYCT substudy focuses on gathering participant-level data to evaluate behavioral determinants of home testing and socio-behavioral mechanisms of SARS-CoV-2 community transmission (Fig. 1). We hypothesize that positive at-home test results will be associated with altered self-reported social interactions and altered health behaviors compared to negative test results. After obtaining informed consent, participants will complete periodic surveys and questionnaires through a smartphone application or call center phone calls. Questionnaires will collect data on demographic characteristics, medical history, health status, COVID testing, symptoms, social interactions, knowledge of prevention strategies, infection risk, and attitudes toward vaccines. We will also ask the participants of the substudy to report the results of their SARS-CoV-2 tests.

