#### Participant support

The at-home testing kits and the marketing campaign included information about a study smartphone application and a Quick Response (QR) code to facilitate access. Developed by CareEvolution, the free app (called MyDataHelps) ran on Apple and Android devices [20]. Serving as a digital study resource, it included information about SYCT, instructions to administer at-home tests for all participants in the public health intervention, and information on how to enroll in the substudy.

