### Behavioral substudy

#### Study population

Adults and children > 8 years of age living within the two communities currently participating in the public health intervention were eligible for the substudy.

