#### Study questionnaires

Those who provide consent and enroll in the substudy are asked to complete questionnaires through an app and report any positive test results. Participants complete surveys and questionnaires through the smartphone app or via the call center according to the schedule of events (Additional file 3)**.** Questionnaires collect data on demographic characteristics, medical history, and health status; SARS-CoV-2 at-home testing and symptoms and any additional PCR testing obtained in response to symptoms; social interactions; knowledge of prevention strategies; infection risk; and attitudes toward vaccines. Questionnaires are completed during the week after each test (regardless of the result). We did not track participant-reported deviations to the recommended SYCT testing protocol.

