#### Questionnaire distribution

The MyDataHelps smartphone application developed by CareEvolution (see ‘SYCT Intervention and Ecological Analysis’ section above) is also being used for the SYCT behavioral substudy [20]. Once registered, if the participant elects to be a part of the substudy, eligibility criteria are verified, and e-consent is obtained through the app. Push notifications are programmed with text messaging to promote adherence, including personalization, context, and timing for all participants in the public health intervention. Additionally, participants can opt-in to reminders for testing three times a week at a time of their preference. For participants who provided consent to the substudy, the app also features the ability to report their test results (upload images of test trips), track testing history, respond to surveys and questionnaires, and access the study team’s contact information.

Alternatively, participants who choose not to use the app can provide their information via phone interviews conducted by a centralized study call center. Using scripted interview guides, call center staff members explain study participation, obtain verbal consent, administer study questionnaires including soliciting test results, and issue phone reminders.

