**Secondary**	
Self-reported data on awareness of the issue, engagement, decisions to act, action, and maintenance	The proportion of respondents who decide to act on precautionary behaviors after a test result for the entire study cohort and stratified by participant demographics (e.g., gender) of interest
Self-reported emergency department visits, hospitalizations, and intensive care unit admission, for SARS CoV-2 evaluation or treatment	Point estimate and 95% confidence interval for each healthcare utilization measure and composite measure for the entire study cohort and stratified by participant demographics (e.g., gender) of interest
Self-reported data on perceptions and prevention of risks of contracting SARS CoV-2 infection	The proportion of respondents who are knowledgeable of precautionary measures to prevent infection for the entire study cohort and stratified by participant demographics (e.g., gender) of interest
Reported results of self-administered SARS CoV-2 antigen test	Prevalence of positive test results with 95% confidence intervals for the entire study cohort and stratified by participant demographic variables of interest

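### The substudy does not limit analysed home-test results to those after consent, so its positivity estimate may be selected on the result

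*Protocol article*

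**What the plan says.** **Entry.** Study design calls the substudy a prospective cohort and states: "Individuals who chose to participate in the SYCT intervention could also enroll in the embedded prospective cohort substudy". Under Behavioral substudy, Study population, the conditions are age and residence: people "living within the two communities currently participating in the public health intervention were eligible for the substudy".

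**Consent.** Questionnaire distribution says: "Once registered, if the participant elects to be a part of the substudy, eligibility criteria are verified, and e-consent is obtained through the app". People who do not use the app give verbal consent to the call center. Neither route is tied to receipt of the kit or to the first test.

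**How people hear of it.** Participant support says: "The at-home testing kits and the marketing campaign included information about a study smartphone application". The same section says the app explains how to enrol.

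**What is reported.** Study design says: "We will also ask the participants of the substudy to report the results of their SARS-CoV-2 tests". Study questionnaires says that enrolees are "asked to complete questionnaires through an app and report any positive test results". The two wordings differ in scope, but neither has a time limit. Study questionnaires also places a questionnaire in the week following each test, whatever its result.

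**Testing after a positive.** Testing protocol tells a person with a positive rapid test to stop testing and pass the remaining tests on within the household.

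**What is estimated.** Table 3 has as a secondary endpoint "Prevalence of positive test results with 95% confidence intervals for the entire study cohort". Its primary endpoint includes the proportion adherent to social distancing after a positive compared with after a negative result. The substudy's sample size section regards 5000 participants as enough to estimate positive-test incidence and prevalence.

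**The concern.** A person can receive a kit, test, learn the result and only then consent. If that result is reported and counted, the chance that a test enters the data may depend on its outcome. Cohort positivity then partly measures how a result affected the decision to join.

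The stopping instruction sharpens this. Someone who joins after a positive would, if the instruction is followed, contribute that positive and no later test.

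The direction is open. Joining may be more likely after a positive, for instance because the app's result-reporting feature is described for consented participants. It may be less likely if people who are positive stop engaging with the programme once testing ends for them.

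The main stake is the Table 3 positivity row, where an interval could look precise around a shifted value. The adherence comparison is at stake only under a further condition, examined in the working.

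**Working it through.** **1. The plan's own figure.** The substudy sample size section gives a 1.5% margin of error for a 50% proportion with 5000 participants at 95% confidence.

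- Half-width: 1.96 × √(0.5 × 0.5 / 5000) = 1.39 points.
- Participants needed for 1.5 points: 1.96² × 0.25 / 0.015² = 4269.

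Since 5000 exceeds 4269, the statement that the sample is sufficient is true. It concerns sampling error only; selection on the result does not shrink as n grows.

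**2. Positivity: inputs.** The article gives none of the first four; they are assumptions.

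- p = 1%: true person-level positivity.
- f = 0.5: share joining after at least one result, before any effect of the result on joining.
- k: chance of joining after a positive relative to joining otherwise; 0.5, 2, 3 or 5.
- g: share of late joiners' positives that predate consent. Only these can have influenced joining.
- n = 5000, from the article.

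For the low end of g, the article gives three tests a week for 4–5 weeks, so 3 × 4 = 12 tests per person at the lower duration. If one of twelve tests precedes joining and positives are spread evenly, g = 1/12. The high end is g = 1.

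**3. Positivity: formula.**

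Weight on positives: w = (1 − f) + f[(1 − g) + gk].

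Observed positivity = pw / (pw + 1 − p).

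For k = 3:

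- g = 1: w = 0.5 + 0.5 × 3 = 2.00; 0.0200 / 1.0100 = 1.98%.
- g = 1/2: w = 0.5 + 0.5 × 2 = 1.50; 0.0150 / 1.0050 = 1.49%.
- g = 1/12: w = 0.5 + 0.5 × 14/12 = 1.083; 0.01083 / 1.00083 = 1.08%.

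| k | g = 1/12 | g = 1/2 | g = 1 |
|---|---|---|---|
| 0.5 | 0.98% | 0.88% | 0.75% |
| 2 | 1.04% | 1.25% | 1.49% |
| 3 | 1.08% | 1.49% | 1.98% |
| 5 | 1.16% | 1.98% | 2.94% |

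Share of observed positives from people who joined after that positive = fgk/w. At k = 3 this is 0.125/1.083 = 12%, 0.75/1.50 = 50% and 1.5/2.00 = 75% for the three values of g.

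**4. Against sampling error.** At 1% and n = 5000, the half-width is 1.96 × √(0.01 × 0.99 / 5000) = 0.28 points. This is calculated here; it is not a figure in the article. At k = 3 the excess over 1% is 0.08, 0.49 and 0.98 points, or about 0.3, 1.8 and 3.5 half-widths.

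**5. Adherence comparison.** This conditions on the result.

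- If joining depends on the result alone, the contrast is unchanged: 50% vs 50% stays at 0, and 70% vs 50% stays at 20 points.
- Suppose instead that, among positives only, adherent people are s times as likely to join as non-adherent people. With true adherence a, observed adherence is as/(as + 1 − a). For a = 50%, s = 1.5, 2 or 3 gives 60%, 67% or 75%. A true difference of 0 becomes 10, 17 or 25 points, or 5, 8 or 12.5 points if only half of the positives joined late.
- If adherence affects joining equally in both groups, a null difference stays null and the odds ratio is preserved. A non-null difference can still move: 70% vs 50% with s = 2 in both becomes 82.4% vs 66.7%, 15.7 points. That is ordinary volunteer selection. It needs no knowledge of the result, and a consent-date rule is not aimed at it.

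**The case against.** The strongest reply is that this rests on silence in a condensed article. The schedule of events (Additional file 3) and the full protocol are not shown and may fix the order of consent and testing. The text also has prospective features: surveys follow informed consent, questionnaires follow each test whatever the result, and the app's reporting feature is described for consented participants. App information came through the campaign as well as the kit, so a person could enrol first and test second. The substudy is described as primarily descriptive, and a post-consent rule would not make an opt-in cohort of about 6% (5000/80,000 = 6.25%) representative.

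Much of this stands. It means late joining is left open, not demonstrated. It does not close the gap. The questionnaire rule governs timing after a test, not whether consent came first: a person who tests positive, joins two days later and answers that week complies with it. Reporting through the app after consent does not stop an earlier result being reported. The article cites Additional file 3 for the schedule and measurement frequency, not for entry.

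Two stronger readings are tempting. A reader might infer that, because Testing protocol mentions a voluntary reporting line for Tennessee only, a North Carolina positive was itself a reason to join, so that positivity is inflated. The article describes reporting as not required and says nothing of why people joined. A reader might also infer that the adherence comparison is biased because entry may follow the result. Step 5 of the working shows that this does not follow from selection on the result alone.

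**Conclusion.** As described, people may enrol after learning a home-test result, and reported results are not limited to tests after consent. The Table 3 positivity estimate may therefore be selected on the result, in either direction, and neither sample size nor exact intervals correct that. With 1% true positivity, half joining late and a threefold joining ratio, all assumed, observed positivity runs from about 1.1% to 2.0%. The upper end requires that every late joiner's positive predates consent; if half do, it is about 1.5%. With a joining ratio of 0.5 the estimate falls, to between 0.98% and 0.75%.

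The primary adherence comparison is threatened by late joining only if joining depends on result and behaviour together. That is possible, but nothing in the article shows it. The mixed model described for the substudy handles correlation within participants and households, not this kind of selection.

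The point is a cheap improvement. The article does not support saying that the cohort was in fact selected on results.

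**What to change.** - **Positivity row of Table 3:** count only tests taken after the participant's consent, among participants with at least one such test. Tabulate results dated before consent separately, including any that prompted enrolment.
- **Adherence comparison:** keep the planned analysis and repeat it restricted to post-consent tests as a sensitivity analysis. A restriction suits a sensitivity analysis better here, because positives are likely to be scarce and the bias needs the further condition above.
- **Data needed:** the consent date and each test date, from the app or call-center record.

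The cost is one analysis-set rule, one extra table and one repeated analysis. Enrolment and testing procedures do not change. The downside is fewer positives and wider intervals. The rule removes enrolment selection on the counted result; it does not make the opt-in cohort representative of the community.
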